## Analyses

Statistical analysis will be performed using SPSS statistical software. Primary analysis will use the intention to treat principle, using the last observation recorded for participants who withdraw from the program.

Baseline data will be reported using descriptive statistics for each variable (individual sports related activity and participation goals, GM capacity, aerobic fitness, anaerobic fitness and agility, functional strength, participation and quality of life) to establish any difference between randomised groups. The method of aggregation will depend on the normality of the data and will include the mean and standard deviation (normally distributed data) or the median and interquartile range (non-normally distributed data). If characteristics are not comparable at baseline, they will be modelled as covariates in subsequent analyses in order to adjust their possible confounding effects. Linear mixed models will be used to evaluate the effectiveness of the *Sports Stars* intervention compared to the waitlist control on the primary outcome (COPM). Linear mixed models take into account variation in individuals over time, are able to manage missing data without excluding participants for further analysis and examine changes in the outcomes over time as well as across the two groups. Significance will be set at *p* < 0.05. Residuals of the fitted models will be examined to ensure that all required assumptions are met.

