### Criteria for withdrawal

Participants will be excluded from the study if they fail to attend either their baseline assessment or withdraw prior to the commencement of the immediate *Sports Stars* group. Primary analysis will use the intention to treat principle, using the last observation carried forward for participants who withdraw after commencement of intervention in the immediate *Sports Stars* group.

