### Recruitment

#### Sample size

According to CONSORT guidelines, sample size calculations are based on adequate power for comparison between the effects of the *Sports Stars* program compared to standard care using the COPM immediately post intervention (T2). Data from a previous study investigating the effects of an exercise group aiming to improve physical activity, balance and strength in ambulant children with CP (6–14 years) showed a standard deviation of 1.87/2.88 (intervention/control) [32]. This standard deviation and a mean change of 2 points for performance on the COPM (clinically meaningful difference) were used to calculate sample size. Based on significance (alpha) of 0.05 and 80% power, a minimum sample of 25 participants in each group (50 participants total) will be required. Therefore, 60 participants (30 in each group) will be recruited to allow for 20% attrition.

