**Classification of CP**

Participants will be classified by motor type (spasticity, dyskinesia, ataxia or unclassifiable) and distribution (unilateral or bilateral) [34, 35].c.**Functional mobility:**
*Functional Mobility Scale (FMS)* [36]

Participants will be classified by their ability to walk five, 50 and 500 m, correlating to their ability at home, school and community. Scores range from N (does not apply), to 6 (independent on all surfaces without aids) [36].2.**Outcomes:** Measured for all participants at four time points and compared to baseline and each other:Time one (T1): *zero months*- BaselineTime two (T2): *2 months*- Immediately after immediate interventionTime three (T3): *5 months*- 12 weeks after immediate intervention

For children participating in the waitlist group, an optional fourth assessment will occur:Time four (T4): approximately *8 months*- Immediately after waitlist intervention

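### For children who withdraw, the primary analysis carries the last COPM score forward, which overrides the planned mixed model's handling of their missing data and biases the estimated effect

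*Protocol article*

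**What the plan says.** The protocol article sets the rule for withdrawals in two places. The Analyses section says: "Primary analysis will use the intention to treat principle, using the last observation recorded for participants who withdraw from the program". The Criteria for withdrawal section, also speaking of the primary analysis, says: "using the last observation carried forward for participants who withdraw after commencement of intervention". Neither place calls it a sensitivity analysis.

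The Analyses section then gives the primary outcome (COPM) to a linear mixed model, and one stated reason is that such models "are able to manage missing data without excluding participants for further analysis". The text does not say how the two rules combine.

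The visits are T1 (baseline), T2 (2 months, just after the immediate program) and T3 (5 months, "12 weeks after immediate intervention"). The Sample size section is built on the COPM at T2 and allows for 20% attrition.

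**The concern.** For a child who withdraws, the two rules compete for the same missing scores. If carry-forward is applied first, the mixed model receives a complete record for that child, and the property for which it was chosen no longer matters for that child.

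The filled-in values make strong claims. Before T2 the only score available to carry is baseline, so a child lost before T2 enters the primary comparison with exactly zero change. A child lost between T2 and T3 is recorded as holding the post-program level at 12 weeks, which is what the T3 visit is there to test. Intention-to-treat requires neither value.

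At stake are the primary estimate, the coverage of its interval and, when loss differs between arms, possibly the type I error. Two readings of one plan that give different answers also leave a choice open until the results are known.

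**Working it through.** **Inputs from the protocol (Sample size).** SDs 1.87 (intervention) and 2.88 (control), target difference 2 points, alpha 0.05, power 80%, 25 per group, 30 per group recruited, 20% attrition.

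**Assumptions not in the protocol.** 1.87/2.88 are SDs of change (the text does not say change or score); loss is completely at random; children are independent; the split of loss by arm and time and the waitlist change are as given below.

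**The plan's own figure.** Pooled SD = √((1.87² + 2.88²)/2) = √5.896 = 2.428. Two-sided, this gives 24 per group by the normal formula and 25 by the noncentral t (power 81.4%). The stated 25 is reproduced.

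**Carry-forward at T2.** Let dI and dC be the fractions withdrawing before T2 in the immediate and waitlist arms, mC the mean waitlist change, and 2 the true effect. A withdrawer contributes zero change, so the expected estimate is (1 − dI)(mC + 2) − (1 − dC)mC.

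| dI / dC | mC | Expected estimate (true 2.0) |
|---|---|---|
| 20% / 20% | any | 0.8 × 2 = 1.6 |
| 10% / 10% (half of the 20% falls after T2) | any | 0.9 × 2 = 1.8 |
| 30% / 10% | 1 | 0.7 × 3 − 0.9 × 1 = 1.2 |
| 10% / 30% | 1 | 0.9 × 3 − 0.7 × 1 = 2.0 |

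**Standard errors at 20%/20%, changes 3 and 1.** With carry-forward, the variance of change in an arm is 0.8 × SD² + 0.8 × 0.2 × mean²:
- immediate arm: 0.8 × 3.497 + 0.16 × 9 = 4.24
- waitlist arm: 0.8 × 8.294 + 0.16 × 1 = 6.80
- carry-forward SE: √((4.24 + 6.80)/30) = 0.61
- observed data, 24 per arm: √((3.497 + 8.294)/24) = 0.70
- nobody missing, 30 per arm: √(11.791/30) = 0.63

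**Simulation of T2 change scores** (40,000 trials, 30 per arm, t tests; observed cases stand in for the mixed model, which is reasonable under completely random loss):
- 20%/20%, changes 3 and 1: carry-forward estimate 1.60, mean SE 0.60, empirical spread also about 0.60, coverage 90%, power about 73%. Observed data: 2.00, SE 0.70, coverage 95%, power 79%.
- 30%/10%, changes 3 and 1: carry-forward estimate 1.2, coverage 76%, power about 46%, against 81% on observed data.
- No true effect, 10%/30% loss: the false effect is 0.9 × 1 − 0.7 × 1 = 0.2 if both arms improve 1 point (type I error about 7%) and 0.9 × 2 − 0.7 × 2 = 0.4 if both improve 2 points (about 11%).
- No true effect, equal loss: no bias, type I error about 5%.

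**Check with fitted mixed models** (REML, group by time, random intercept; SD 2.43 at each visit, within-child correlation 0.5, effect constant to T3; 1,500 trials per scenario). At 20%/20% before T2 with no waitlist change:
- Observed data: estimate 2.02, SE 0.68, coverage 94%, power 83%.
- After carry-forward: estimate 1.60, SE 0.57, coverage 88.5%, power 78%.

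With half the loss after T2 (waitlist change 0.5), carry-forward gives 1.81 at T2 and 1.82 at T3. With no true effect, a 1-point change in both arms and 10%/30% loss, the false T2 effect is 0.17 with about 5% rejections, so the type I inflation at a 1-point change is slight.

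**T3 illustration (assumed).** If the immediate arm's gain fades from 2 to 0, the waitlist arm does not change, and 20% of immediate-arm children leave after T2, carry-forward reports 0.8 × 0 + 0.2 × 2 = 0.4 where the truth is 0.

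**The case against.** Several points on the other side stand.

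- **Scope.** Both sections limit carry-forward to children who withdraw. A reader might infer that the mixed model never gets to handle missing data at all. The text does not support that: a T2 or T3 visit missed without withdrawal is not filled in and stays with the model. The conflict concerns withdrawers only.
- **Standard error.** A reader might also infer a second, separate fault, that carry-forward makes the standard error wrong. It does not. The carry-forward SE agrees with that estimator's own sampling spread, and type I error stays near 5% with no effect and equal loss. The undercoverage comes from the bias. What remains is that 0.60 is smaller than the 0.62 to 0.63 expected with no child lost, so it understates uncertainty about the true effect.
- **Size and direction.** The protocol gives one overall attrition figure, not by arm or time. Putting all of it before T2, within a two-month window, is the harsher case. With equal loss the bias is towards no effect, which is conservative for a superiority trial. With a true effect of 2 and a waitlist change of 1, the estimate is 2 − 3dI + dC, so inflation needs waitlist loss above three times immediate-arm loss. The unequal splits and the fading gain at T3 are illustrations.
- **Loss mechanism.** Completely random loss favours the observed-data model. If withdrawal depends on unseen outcomes, that model is biased too.

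None of this reconciles the two rules for a withdrawing child or makes zero change a sound value for a missing T2 score.

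**Conclusion.** The point holds for withdrawers. The plan places carry-forward inside the primary analysis, where it displaces the model's own treatment of those children and biases the estimate. Under the protocol's 20% attrition, equal between arms, a true 2-point effect becomes 1.6 if all loss precedes T2 and about 1.8 if half follows it. These two figures need no assumption about the SD or the waitlist change. In the first case coverage is about 90% and power about 73% against 79%, reading 1.87/2.88 as SDs of change.

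Under assumed unequal loss the bias may be larger (1.2 at 30%/10%), cancel (2.0 at 10%/30%) or create a false effect of 0.2 to 0.4 points, with type I error of about 7% to 11% in the change-score calculation. The direction cannot be known in advance, so carry-forward cannot be defended as reliably conservative.

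**What to change.** Delete carry-forward from the primary analysis in both Criteria for withdrawal and Analyses. State that the planned COPM mixed model is fitted by restricted maximum likelihood to all observed T1, T2 and T3 scores, without imputation, including the scores that withdrawers gave before leaving. If carry-forward is kept, label it a sensitivity analysis, preferably beside a delta-adjusted one that shifts the missing scores by a fixed amount in each arm.

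The cost is a change of wording and a small amount of analysis, with no new data and no new model. The standard error becomes somewhat larger (about 0.70 instead of 0.60 at 20% loss), and the primary result rests on data being missing at random, which the delta-adjusted analysis would probe.

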### Outcome measures and procedures

All outcomes will be collected pre-intervention, immediately post intervention and at 12 weeks post intervention by the blinded chief investigator (GC).Classification of Sample

Participants will be classified based on their severity and age to compare groups at baseline. They will be classified according to:**Gross motor function:**
*Gross Motor Functional Classification System (GMFCS-E&R)* [33]

The Gross Motor Function Classification System is an internationally recognized classification system for children and youth with CP. Participants will be classified as either classified as GMFCS- E&R I (able to walk independently at home, school, outdoors and in the community with limitations in speed, balance or coordination) or II (able to walk in most settings, however may have difficulty with distances or more challenging environments and gross motor skills like running and jumping) using the descriptors for between the child’s 6th and 12th birthday [33].b.

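### Covariates enter the primary COPM model only if the arms are judged unbalanced at baseline, with no criterion, so the model depends on chance and on judgement after arm-level data are seen

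*Protocol article*

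**What the plan says.** The Analyses section has baseline data summarised by arm "to establish any difference between randomised groups". The variables are "individual sports related activity and participation goals, GM capacity, aerobic fitness, anaerobic fitness and agility, functional strength, participation and quality of life", which is seven domains. Under Outcome measures and procedures, the classification variables are added: "Participants will be classified based on their severity and age to compare groups at baseline".

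The rule then follows: "If characteristics are not comparable at baseline, they will be modelled as covariates in subsequent analyses in order to adjust their possible confounding effects". The next sentence of the Analyses section introduces linear mixed models for the primary outcome, the COPM, so the primary analysis is among those the rule governs. The article states no threshold, test or size of difference that would make a characteristic count as unbalanced, and names no covariate that enters in every case.

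T1 (baseline) is listed as one of the measurement times, and the section gives as a reason for the method that "Linear mixed models take into account variation in individuals over time". It does not say whether T1 COPM is a response, a covariate or both, or whether the arms share a common T1 mean.

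**The concern.** The arms are formed by randomisation, so a baseline difference between them is a chance event. Its size says nothing about whether the variable predicts the COPM. A rule that selects on observed imbalance can admit a variable with no bearing on the outcome and omit a prognostic one that happens to look balanced.

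Two things are at stake. First, with no criterion, the primary model is settled by judgement after the baseline data have been seen by arm, from a sizeable pool: seven domains, several with more than one measure (functional strength alone has three tests), plus age and the severity classifications. Second, a covariate that predicts the outcome improves precision whether or not the arms differ on it, and most of that gain is lost if it is used only when an imbalance appears.

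This is not a detail left to a fuller plan. The article states a rule, and the rule is poor.

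**Working it through.** **1. The plan's own sample size.** Inputs from the Sample size section: "Based on significance (alpha) of 0.05 and 80% power"; "showed a standard deviation of 1.87/2.88 (intervention/control"); "a mean change of 2 points for performance on the COPM (clinically meaningful difference"). Two-sided testing is assumed.

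- Pooled SD = √[(1.87² + 2.88²)/2] = √5.896 = 2.428.
- n per arm = 2 × (1.96 + 0.842)² × 2.428² / 2² = 23.1, so 24 by the normal approximation.
- With the t distribution, 24 per arm gives 79.8% power and 25 gives 81.4%.

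The stated 25 per group is reproduced. It is an unadjusted two-group comparison and assumes no covariate.

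**2. How often chance would trigger the rule.** The documents give no criterion, so p<0.05 is assumed here, with independent variables.

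- Seven variables: 1 − 0.95⁷ = 30%.
- Ten variables: 1 − 0.95¹⁰ = 40%.

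Gross motor capacity, fitness, agility and strength are likely to be positively correlated, which lowers these figures. Whole groups of four to six children are allocated together, and any similarity within groups would raise them. Neither effect can be sized from the documents.

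**3. What the rule does to one covariate.** The documents give no covariate-outcome correlation, so ρ is assumed to be 0.3, 0.5 or 0.7. Simulation: 40,000 trials for each setting, 25 per arm, SD 2.428, a single post-treatment contrast, one covariate, and adjustment under the rule only if the baseline p<0.05.

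| | ρ = 0.3 | ρ = 0.5 | ρ = 0.7 |
|---|---|---|---|
| Type I error, conditional rule | 4.8% | 4.3% | 3.6% |
| SD of estimate, never adjusted | 0.687 | 0.687 | 0.685 |
| SD of estimate, conditional rule | 0.679 | 0.667 | 0.639 |
| SD of estimate, always adjusted | 0.660 | 0.601 | 0.493 |
| Power at 2 points, never adjusted | 82% | 82% | 81% |
| Power at 2 points, conditional rule | 82% | 83% | 83% |
| Power at 2 points, always adjusted | 84% | 90% | 98% |

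At ρ = 0.5 the rule recovers (0.687 − 0.667)/(0.687 − 0.601) = 0.020/0.086, or about a quarter of the available reduction in SD. The test is slightly conservative, not inflated. This is a simplified setting and not the planned longitudinal model. It shows the direction of the effect and should not be read as a power figure for this trial.

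**4. What is at stake for baseline COPM in the planned model.** Let r be the T1-T2 correlation, assumed to be 0.4 to 0.6, with equal variances at the two times.

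- Unconstrained group-by-time contrast: it behaves like a change score, with variance factor 2(1 − r). Baseline adjustment has factor 1 − r². The ratio is (1 + r)/2 = 0.70, 0.75 and 0.80 at r = 0.4, 0.5 and 0.6, a reduction of 30%, 25% and 20%.
- Common T1 mean for both arms: baseline COPM is already used efficiently, and the gain is about 0%.

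The article does not say which form applies, so the range for the COPM itself is about 0% to 30%.

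**The case against.** The best defence is that baseline COPM is probably in the model already. The article describes a longitudinal mixed model with T1 as a measurement time, so T1 COPM is most naturally a repeated response, present whatever the balance. This stands. It rules out a tempting calculation: against a comparison of T2 scores alone, baseline adjustment at r = 0.4-0.6 cuts variance by 16-36% (r²), equivalent to 19-56% more children (1/(1 − r²) − 1). The plan does not describe a T2-only analysis, so those figures do not apply.

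A reader might also infer that choosing covariates after looking at the data inflates the false-positive rate. The documents do not support that, and the simulation of a mechanical single-covariate rule gives an error slightly below 5%. The simulation does not cover discretionary choice among many covariates, which the open wording permits, but no inflation has been demonstrated.

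Nor do the documents show how often the rule would fire. The article promises descriptive statistics and states no significance screen, so the 30% illustrates one possible criterion. Classifying children by severity and age to describe the arms is ordinary reporting and is not itself a fault.

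Finally, nothing in the article shows that GMFCS level or age predicts COPM ratings of individually chosen goals. Which covariates to fix is partly a clinical judgement. That affects the contents of the list, but it is not a reason to let observed imbalance choose it.

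**Conclusion.** The point holds as a weakness in a stated rule. Covariates enter the primary COPM model on an undefined judgement of imbalance, so the model is open to chance and to choice after arm-level data are seen, and most of the precision from prognostic baseline variables is forgone.

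The size is moderate and partly unknown. For the COPM itself the variance gain from fixed adjustment is about 0% or 20-30%, depending on a model form the article leaves open and on an assumed r of 0.6-0.4. For other covariates it depends on prognostic strength, on which the documents give nothing. The 30% trigger rate assumes a p<0.05 criterion and independent variables.

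The trial's validity is not threatened by this rule, but it should be changed because the replacement is better and nearly free.

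**What to change.** Replace the sentence with a prespecified primary model:

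- Include baseline COPM performance, either as a covariate or through a common T1 mean for the two arms, and say which.
- Add a short fixed list, such as GMFCS level (I or II) and age, in every analysis whatever the observed balance. If T1 stays in the model as a response with separate arm means, give these covariates time-specific effects, because an effect common to all visits cancels out of a within-child change.
- Fit location pair as a random effect, or accept its cost as a fixed factor. Sixty children in groups of four to six make about 10 to 16 groups, hence 5 to 8 pairs and 4 to 7 extra degrees of freedom.
- Report baseline data by arm descriptively, without a judgement of comparability, and keep imbalance-driven adjustment as a sensitivity analysis only.

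All these variables are already collected or known from recruitment, so no visits, measures or children are added. The cost is a few sentences of text and about three model degrees of freedom for the fixed covariates, besides whatever location pair uses. The change should be made before any outcome data are seen by arm.

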### Primary hypothesis

**H1:** Compared to children in the standard care group, children in the *Sports Stars* group will demonstrate greater improvement in their individually-selected, sports activity and participation related goals measured by the Canadian Occupational Performance Measure (COPM).

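### Baseline adjustment is conditional and its form is unstated; on the most natural reading of the mixed model it leaves the primary COPM contrast unchanged

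*Protocol article*

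**What the plan says.** The Analyses section sets a conditional rule. Where the arms are found to differ in their baseline characteristics, "they will be modelled as covariates in subsequent analyses in order to adjust their possible confounding effects". The variables examined at baseline are "individual sports related activity and participation goals, GM capacity, aerobic fitness, anaerobic fitness and agility, functional strength, participation and quality of life". The individual goals are what the COPM measures, so the baseline of the primary outcome is on the list.

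The same section names the primary model ("Linear mixed models will be used to evaluate the effectiveness of the" intervention on the COPM) and says that such models "examine changes in the outcomes over time as well as across the two groups". It gives no response vector, fixed effects or covariate form.

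Three other statements bear on the reading:
- The primary hypothesis is one of change: the intervention "group will demonstrate greater improvement in their individually-selected, sports activity and participation related goals".
- The outcome schedule, under Outcome measures and procedures, describes outcomes as "Measured for all participants at four time points and compared to baseline and each other".
- Withdrawals are handled by "using the last observation recorded for participants who withdraw from the program", which would leave analysed children with complete T1 to T3 data.

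**The concern.** The rule makes a positive promise: where the arms differ at baseline, a covariate will deal with the confounding. Whether it does depends on where T1 COPM sits in the model.

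The text points towards T1 as a response. Covariates enter only if an imbalance is seen, so in a balanced trial T1 COPM would not be a covariate. A mixed model of COPM can then measure improvement from baseline only if T1 is among the responses. The rule adds a term when it is triggered; nothing says that T1 then leaves the response. The ordinary sense of a covariate, with no interaction mentioned, is a main effect.

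Under that specification the added term cannot move the arm-by-time contrast. The report could then say that a T1 imbalance had been adjusted for when the primary estimate was the same as without adjustment. Allocation makes an imbalance more than a remote possibility: whole groups of four to six children are randomised in pairs by coin flip (Recruitment process; Randomisation).

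**Working it through.** **Inputs from the protocol article.** SDs 1.87 and 2.88, target 2 points, alpha 0.05, power 80%, 25 per group required and 30 per group recruited (all Sample size).

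**Assumed, not in the document.** Correlation rho between T1 and T2 COPM of 0.3, 0.5 or 0.7; equal SDs at T1 and T2; independent children; a T1 imbalance of 1 point; a true effect of 2.

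**1. The plan's own figure.** Pooled SD = sqrt((1.87² + 2.88²)/2) = sqrt(5.896) = 2.428. With a two-sided alpha, n per group = 2 × (1.960 + 0.842)² × 5.896 / 2² = 23.1, so 24 by the normal approximation. The t-test gives 24.1, so 25. The stated 25 reproduces. It does not bear on the point, but it supports a working SD of about 2.4.

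**2. Cancellation.** Write the mean of child i at visit t as m(t) + d(t) × arm(i) + b × x(i), where x is a baseline covariate. The covariate adds the same b × x(i) at T1, T2 and T3. With complete data and a free mean for each arm and visit, it shifts d(1), d(2) and d(3) equally, so d(2) - d(1) is unchanged. In 400 simulated trials per rho, the estimates with and without a main-effect covariate differed by less than 1e-13. This held for a separate baseline measure under unstructured and compound-symmetry covariance, and for T1 COPM itself under compound symmetry.

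**3. Error given an imbalance D at T1 (intervention minus control).** The expected T2 difference is 2 + rho × D. Subtracting D gives 2 - (1 - rho) × D, so the error is -(1 - rho) × D. Simulated mean estimates at T2 for D = 1 and a true effect of 2:

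| Model | rho 0.3 | rho 0.5 | rho 0.7 |
|---|---|---|---|
| Expected, 2 - (1 - rho) | 1.30 | 1.50 | 1.70 |
| T1 a response, no covariate | 1.25 | 1.49 | 1.70 |
| T1 a response, main-effect covariate | 1.25 | 1.49 | 1.70 |
| T1 a response, another baseline measure × time | 1.72 | 1.85 | 1.90 |
| T1 a covariate, T2 the response | 1.95 | 2.00 | 2.00 |
| T1 a response, common T1 mean | 1.95 | 2.00 | 2.00 |

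The error is 0.7, 0.5 and 0.3 points, or 35%, 25% and 15% of the 2-point target.

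**4. How often D reaches 1 point.** SE of the T1 difference = 2.4 × sqrt(2/30) = 0.62. Then 1/0.62 = 1.61, and a difference of 1 point or more in either direction has probability about 11%. With an SD of 1.87 (SE 0.48, ratio 2.07) it is about 4%; with 2.88 (SE 0.74, ratio 1.34) about 18%.

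**5. Precision, SD 2.4 and 30 per arm.** The change contrast has SE = 2.4 × sqrt(2(1 - rho)) × sqrt(2/30). Baseline adjustment has SE = 2.4 × sqrt(1 - rho²) × sqrt(2/30).

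| | rho 0.3 | rho 0.5 | rho 0.7 |
|---|---|---|---|
| Change contrast | 0.73 | 0.62 | 0.48 |
| Adjusted for T1 | 0.59 | 0.54 | 0.44 |

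**The case against.** The strongest reply is that the specification is inferred. The article never lists the responses, never says that the effect is the arm-by-time term, and never confines covariates to main effects. The remark about comparing with baseline sits in the measurement schedule, not in the model description. Model terms are commonly left to a full protocol or SAP, so silence about them is not a fault. This stands: a reader might infer that the planned adjustment can never work, and the document does not support that. If the sponsor means T1 as a covariate with T2 and T3 as responses, the adjustment works fully; with covariate-by-time terms it works at least in part.

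A reader might also infer that the whole imbalance remains in the treatment effect. It does not. The contrast already subtracts the T1 difference, and only the regression-to-the-mean part is left, with the opposite sign.

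It is also fair to say that the change contrast is unbiased over randomisation, so using it is not an error in itself. The figures rest on an assumed correlation and on an SD that the Sample size section does not identify as that of scores or of change.

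What the reply does not answer is that the article does fix something: adjustment only on observed imbalance, with a stated purpose. On the reading that best fits the rest of the text, that purpose is not met.

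**Conclusion.** The point holds as a conditional one. If T1 COPM is a response, the primary hypothesis is read from arm-by-time, and covariates are main effects, the promised adjustment has no effect on the T2 contrast. This is exact with complete data. What then remains is an error of about (1 - rho) times the T1 imbalance, opposite in sign and possible in either direction, together with a larger SE than baseline adjustment would give.

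The sizes rest on equal SDs at T1 and T2, an SD near 2.4 applied to T1 scores, the assumed correlations and independent children. Correlation within the randomised groups would make a 1-point imbalance more likely; it was not modelled.

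A reader might further infer that the effect would be diluted by averaging the arm difference over all visits, including the untreated T1 row. The document does not support this: the primary hypothesis concerns improvement, and the sample size is set for T2.

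The change is worth making whichever specification was intended, because it replaces a data-dependent rule with a more precise analysis that uses a value already collected.

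**What to change.** In the Analyses section, replace the conditional rule for the primary outcome with adjustment for T1 COPM in all children, whatever imbalance is observed. Make T2 and T3 COPM the only responses; take arm, visit, arm × visit, T1 COPM and T1 COPM × visit as fixed effects; read the primary hypothesis from the arm effect at T2. Equivalently, keep T1 as a response and constrain the arms to a common T1 mean. T1 COPM should not be both a response and a covariate.

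Any other baseline covariate should enter in a form that can affect the T2 contrast; if T1 is kept as a response, that means with its visit interaction.

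The cost is one or two sentences of model wording. It needs no extra children, visits or data, and the planned software can fit it.
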